#### • Electromyography sensor – EMG

The electromyography sensor, placed on the surface of the skin, directly above the forearm's muscles, detects small electrical current or signals that comes from active muscles registering the muscle tension.

#### • Blood Volume Pulse sensor – BVP

The BVP is a pulse detection sensor housed in a small finger worn package, to measure pulse rate of subject. The BVP sensor uses photoplethysmography to detect the blood pressure in the extremities. Photoplethysmography is a process of applying a light source and measuring the light reflected by the skin. At each contraction of the heart, blood is forced through the peripheral vessels, producing engorgement of the vessels under the light source, thereby modifying the amount of light to the photosensor. The resulting pressure waveform is recorded.

#### • Respiration sensor

The Respiration sensor is an easy fitting high durability latex rubber band fixed with velcro belt for monitoring respiration rate from a subject. The sensor is strapped to the torso to measure the relative amount of expansion that occurs during respiration (breathing). As breathing in takes place the rib cage expands which stretches the device. When exhaling, the stretch relaxes and the sensor returns to its neutral position. The resulting waveform is displayed on the screen.

#### • Skin Conductance Response sensors – SCR

The Skin Conductance Response is a measure of the skin's conductance between two electrodes. Electrodes are small metal plates that apply a safe, imperceptibly tiny voltage across the skin. They are typically attached to the subject's fingers or toes using electrode cuffs or to any part of the body using a silver-Chloride electrode patch. To measure the resistance, a small voltage is applied to the skin and the skin's current conduction is measured. Skin conductance is considered to be a function of the sweat gland activity and the skin's pore size. An individual's baseline skin conductance varies for many reasons, including gender, diet, skin type and situation. Sweat gland activity is controlled in part by the sympathetic nervous system. When a subject is startled or experiences anxiety, there will be a fast increase in the skin's conductance (a period of seconds) due to increased activity in the sweat glands (unless the glands are saturated with sweat). After a startle, the skin's conductance will decrease naturally due to reabsorption. There is a saturation to the effect: when the duct of the sweat gland fills there is no longer a possibility of further increasing skin conductance. Excess sweat pours out of the duct. Sweat gland activity increases the skin's capacity to conduct the current passing through it and changes in the skin conductance reflect changes in the level of arousal in the sympathetic nervous system (see figure 1).

**Figure 1 F1:**
[figure not shown]
**The Procomp Infiniti System**. a) the Procomp Infiniti control box; b) the Skin Conductance Response sensors; c) the Electromyography sensor; d) the Blood Volume Pulse sensor; e) the Respiration sensor.

### Data collection

Epidemiological, clinical and all outcome data from each patient will be recorded by the clinician responsible of the study in an electronic database. Psychophysiological data from the Procomp Infinity System will be transformed and recorded in Excel files.

At the end of the treatment, clinicians will arrange a 6 and 12-month review appointment with the patients in the intervention groups and a 12-month review for those in the WL group. At those points clinical follow up data will be collected. A reminder of forthcoming appointments will be distributed to each participant practice 2 weeks before the appointment is due.

### Experimental design

Patients included in the study will be randomly assigned to one of the following three conditions:

(I) VR: subjects will be taught to relax using VR relaxing environments and audio-visual mobile narratives;

(II) non-VR: patients will be taught to relax using the same relaxing narratives proposed to the VR group, but without the VR support;

(III) WL: patients included in the waiting list group will not receive any kind of relaxation training.

Psychometric and psychophysiological outcomes will serve as quantitative dependent variables, while subjective reports of participants will be used as qualitative dependent variables.

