### Subjects

Patients will be recruited in a public health-care structure in Milan, Italy, according to the diagnosis received from their treating responsible psychiatrist or psychologist. In order to be included in the study, patients have to meet the following criteria: (1) primary diagnosis of GAD; (2) requesting treatment for their GAD; (3) older than 17 and younger than 70; (4) no depressive disorder preceding the current episode of GAD or requiring immediate treatment; (5) no behaviour therapy received for their GAD; (6) no evidence of organic mental disorders accounting for the complaints, mental retardation, psychotic disorders, alcohol or drug dependence; (7) no migraine, headache, seizure disorder, and vestibular abnormalities since they represent significant contraindications for the use of VR.

A power analysis was conducted in order to evaluate the number of patients needed to detect a significant difference (Effect size f ≥ 0,40) between the three groups (VR, non VR and WL) with a power of 0,90. The analysis showed a necessary total sample size of 75, 25 in each group, with α = 0,5, two-tailed. Both males and females will be included. All participants have to be clinically stable, meaning no change in dose of psychotropic medications 1 month before inclusion. Since over 90% of individuals who meet criteria for GAD in a given year will also have at least one other DSM-IV diagnosis [8], patients will be included in the study even if they present at least one more psychiatric diagnosis.

Before participating in the study, each patient will be provided with written information about the study and invited to give written consent for inclusion. The present research is in compliance with the Helsinki Declaration.

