### Psychometric assessment

The following psychometric questionnaires will be administered to each patient at pre-treatment, upon completion of the clinical trial, and after 6-month and 12-month follow-up periods:

- PSWQ – Penn State Worry Questionnaire – [18]. The PSWQ is the only existing questionnaire specific for GAD with an extensive validation on Italian population. It analyzes symptoms of pathological worries that characterize this disorder.

- BAI – Beck Anxiety Inventory – [19]. The BAI is a standardised and well-used assessment measure with good psychometric properties used to assess anxiety. It is a 21-item scale which covers cognitive, behavioural and physiological symptoms of anxiety.

- Anti – Anxious Thoughts Inventory – [20]. The AnTI included 22 items that investigate 3 different categories of worries: social worries, worries linked to health and the metacognitions about worry (fear of fear). The available data show that the AnTI questionnaire is sensitive to treatment effects.

- CID – Anxiety and Depression Scales of the Clinical Interview for Depression – [21]. The CID anxiety scale consists of 4 items rated on a 7-point scale. The CID depression scale includes 10 items.

- STAI – State-Trait Anxiety Inventory – [22]. The STAI measures a person's situational (or state) anxiety, as well as the amount of anxiety a person generally feels most of the time (trait). The two scales contain 20 items each, which may be scored 1 (not at all) to 4 (very much so).

Immediately before and after each treatment session subjects will be also asked to rate their levels of subjective anxiety on the Visual Anxiety Scale (VAS-A). In order to verify if there is a positive correlation between the treatment efficacy and the sense of presence experienced by the patients during the treatment sessions, the Itc-Sense of Presence Inventory (ITC-SOPI) [23] will be administered to each patient exposed to the VR environment after each session. The ITC-SOPI is a questionnaire composed by 44 items, that investigates the sense of presence experienced during the VR exposure.

Moreover, as homework, patients will be asked to fill some forms regarding their relaxing experiences.

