### Trial analysis

Data will be entered in SPSS. Descriptive methods will be used to demonstrate the consistency of the three groups, describe participant characteristics and report levels of participation and drop out. Analysis of variance will be used to evaluate baseline characteristics of the three groups involved in the study, overall significance of improvement across outcome measures, and drop out versus maintainers. For each patient, change in psychometric and physiological measures will be calculated and analysed using t-test for matched groups for both intervention and control groups. The magnitude of change will be estimated and the 95% confidence intervals given.

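### No primary outcome, time point or contrast is named, and the power statement refers to no scale and not to the VR versus non-VR comparison of hypothesis I

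*Protocol article*

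**What the plan says.** - **Outcomes.** Experimental design: "Psychometric and psychophysiological outcomes will serve as quantitative dependent variables". No order of importance is given there or elsewhere.
- **Instruments and visits.** Psychometric assessment lists PSWQ, BAI, AnTI, CID and STAI, given before treatment, at completion, and at 6 and 12 months. VAS-A is rated around each treatment session. Psychophysiological assessment adds muscle tension, heart rate, respiration and skin conductance, also around sessions.
- **The one remark that sets a scale apart.** Psychometric assessment: "The PSWQ is the only existing questionnaire specific for GAD with an extensive validation on Italian population". It describes the instrument and does not make it primary.
- **Sample size.** Subjects gives "Effect size f ≥ 0,40) between the three groups (VR, non VR and WL", "with a power of 0,90", a "necessary total sample size of 75, 25 in each group" and "with α = 0,5, two-tailed". No scale, visit or standard deviation is mentioned.
- **Analysis.** Trial analysis uses analysis of variance for "overall significance of improvement across outcome measures" and matched t-tests on change in the psychometric and physiological measures. It adds: "The magnitude of change will be estimated and the 95% confidence intervals given".
- **Hypothesis I** (Aim of the study) compares patients exposed to the VR environment with patients given the traditional relaxation protocol.

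**The concern.** A sample size is calculated for an outcome, at a time, for a contrast. Here none of the three is identified. The measures are unranked and the analysis runs across all of them, so the document has no rule for which result decides whether VR helped. A trial with one significant scale out of many could be reported as positive, and nothing in the plan would contradict that.

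The power statement has a second problem. It concerns a difference among three groups including the waiting list, whereas the scientific question is VR against non-VR. A reader could take 0.90 as the chance of answering that question, but it is not. Nor can the three-group figure refer to VAS-A or the physiological signals as described: they are taken around treatment sessions, and the waiting-list group receives no relaxation training.

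**Working it through.** **1. The plan's own figure.** Inputs from Subjects: k = 3, N = 75, f = 0.40. Noncentrality λ = N·f² = 75 × 0.16 = 12, with 2 and 72 degrees of freedom.
- At α = 0.05 the power is 86.9%; reaching 90% in equal groups needs 84 patients (28 per group).
- At α = 0.5 as printed the power is 99.4%, and 30 patients would suffice for 90%.

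The stated 75 does not reproduce exactly either way. I use α = 0.05 below as an assumption, because the 95% intervals in Trial analysis point to it. The printed value is a separate matter.

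**2. How many scales.** Psychometric assessment supports five questionnaires, or seven scales if CID (anxiety, depression) and STAI (state, trait) are each split in two. Both intervention groups are followed at completion, 6 and 12 months, so there are three post-baseline occasions.

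**3. Chance of at least one false positive, independent tests.** The formula is 1 − 0.95^m.
- m = 5: 1 − 0.95⁵ = 22.6%
- m = 7: 1 − 0.95⁷ = 30.2%

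**4. The same with correlated scales.** Simulation of VR against non-VR: 25 per arm, two-sample t-tests at two-sided 0.05, no true effect, 40,000 to 100,000 runs per cell in the main check (20,000 for five scales over three occasions at 0.5). The between-scale correlation and the occasion correlation of 0.6 are assumptions.

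| Scales × occasions | r = 0.3 | r = 0.5 | r = 0.7 |
|---|---|---|---|
| 5 × 1 | 21% | 18% | 15% |
| 7 × 1 | 27% | 23% | 18% |
| 5 × 3 | 44% | 39% | 33% |
| 7 × 3 | 54% | 47% | 38% |

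The most favourable cell is three times the nominal 5%. VAS-A and the four physiological signals are not counted and would add to these figures.

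**5. What f = 0.40 implies for VR minus non-VR.** f is the standard deviation of the three group means in units of the within-group SD.
- Both relaxation arms equal, waiting list apart by δ: f = δ√2/3, so δ = 0.40 × 3/√2 = 0.85 SD. VR minus non-VR is **0**.
- Equally spaced, non-VR midway: f = δ√(2/3), so δ = 0.40/0.816 = **0.49 SD**.
- Waiting list midway between the two relaxation arms: the largest possible gap, 2 × 0.49 = **0.98 SD**.

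**6. Power of 25 per arm for that contrast.** Two-sample t-test, two-sided 0.05, 48 degrees of freedom, noncentrality d·√(25/2) = 3.536·d.
- d = 0.49: noncentrality 1.73, power about 40%
- d = 0.80: noncentrality 2.83, power about 79%
- d = 0.98: noncentrality 3.47, power about 92%

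So 0.90 is reached only close to the extreme in which the waiting list lies between the two active arms.

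**The case against.** The case on the other side has several sound parts.

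- **A multiplicity method may be in an analysis plan that is not shown.** This stands, and the absence of such a method is not the point. What the article itself fixes is an unranked set of outcomes and a sample size tied to none of them. Choosing the outcome for which a trial is sized belongs to the protocol.
- **α = 0.05 is not in the text.** This stands. It is labelled here as an assumption.
- **The simulated tests are not the ones specified.** This stands in part. Trial analysis names analysis of variance and matched t-tests, not a VR versus non-VR t-test per scale and visit. The percentages therefore describe a scenario: what happens if hypothesis I is examined scale by scale. Three-group analysis of variance at 0.05 gives much the same at one occasion: 15–27% for five to seven scales at correlations of 0.3–0.7.
- **The power can be checked.** This stands. f is standardised, and the calculation was checked above without a scale. What cannot be judged is whether 0.40 is plausible for any particular score.
- **PSWQ is not the only candidate.** This stands. The stated aim is to reduce anxiety, and BAI and STAI measure anxiety while PSWQ measures worry.

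A reader might go further and count at least nine scores by splitting AnTI into its three worry categories, giving 1 − 0.95⁹ = 37%. The article says the items cover three categories, but not that these are scored or tested separately.

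**Conclusion.** The point holds. No primary outcome, time point or contrast is named, and the power statement belongs to no measure and to a three-group difference rather than to VR against non-VR.

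The size depends on α = 0.05 and on scale-by-scale testing of VR against non-VR, both assumed. At one occasion the chance of at least one false positive is 23–30% for independent scales and about 15–27% at correlations of 0.3–0.7. Over three occasions, with an occasion correlation of 0.6, it is about 33–54%.

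A reader might infer that a false positive is likely, in the sense of more probable than not. The figures do not support that at a single occasion. Over three occasions, among the correlated cases shown, only seven scales with low correlation pass one half. The inflation is several times 5%, which is enough to require a change.

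**What to change.** Before any data are seen:

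1. Name one questionnaire score at end of treatment as the primary outcome. PSWQ is one defensible choice, given what Psychometric assessment says of it; the essential step is to name one.
2. Name VR minus non-VR as the primary contrast, in line with hypothesis I.
3. Label all other scales, the 6- and 12-month visits, VAS-A and the physiological signals as secondary or supportive. How the secondary tests are adjusted can be left to the analysis plan.
4. Do not move the 0.90 to the new contrast. State the power that 25 per arm gives for it over a range of differences (about 40% at d = 0.49, 79% at d = 0.8, two-sided 0.05), and state the intended α.

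**Cost.** No new measurement is needed; the change is protocol wording plus a recalculated power statement. A positive result on another scale alone would no longer count as proof. The stated power becomes less favourable, which may reopen the sample size.

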### Randomization

The present trial is a randomized controlled trial. Patients will be randomly assigned to one of the three groups of treatment using numbers generated at random [24].

### Hardware

The VR system is composed by (see figure 2):

**Figure 2 F2:**
[figure not shown]
**The virtual reality equipment**. a) the Head Mounted Display, Sony Glasstron PLM S-700; b) the position tracker, Intersense Intertrax2 256 Hz.

- a laptop (Asus G2S; Intel^® ^Core™2 Extreme Processor X7800);

- an Head Mounted Display (HMD), Sony Glasstron PLM S-700, equipped with a visual device for a 3D view of the virtual environment and an audio device (earphones) to listen to the narratives;

- a position tracker, Intersense Intertrax2 256 Hz, that allows the user to modify his/her point of view in the virtual environment according to his/her movements in the real world;

- a joystick.

The iRiver Clix, a portable audio-visual device, will be assigned to each patient included in the two experimental groups, in order to help him/her to practice the relaxation techniques out of the therapist's office. Patients in the VR group will use it to play video and sound, while the others will use it just to listen to the narratives.

### The virtual environment software

In the present protocol we will use two different virtual environments included in the open-source software NeuroVR (version 1.5) [25].

For the relaxation sessions, the Green Valley, a very relaxing environment showing a mountain landscape around a calm lake is presented together with the relaxing narrative and soft sounds (birds' songs, water flowing, etc) (see figure 3). Patients are asked to walk around the lake, to observe the nature and, after few minutes, to virtually seat on a comfortable deck chair, in order to become easily relaxed.

**Figure 3 F3:**
[figure not shown]
**A screenshot from NeuroVR (V. 1.5)**. The Green Valley is the virtual environment used to facilitate relaxation in the VR group.

For the second part of the protocol, patients will be presented with specific stressful virtual environments that simulate real-life situations: a crowded place, a classroom, an apartment, and so on (see figure 4). Each of these environments can be modified by the therapist with objects, persons and multimedial components depending on the patients' needs.

**Figure 4 F4:**
[figure not shown]
**A screenshot from NeuroVR (V. 1.5)**. The figure illustrates a virtual kitchen, one of the stressful environments showed to the patients during the last week of treatment.

### Clinical protocol

The clinical protocol will be based on 7 weeks of Applied Relaxation (AR) training (2 sessions per week). Patients will be taught coping skills which enable them to relax rapidly, in order to counteract and possibly eliminate the anxiety reactions.

We will now describe the protocol in details, following the one developed by Ost in 1987 [26]. The sessions will be the same for both groups (VR and non-VR), with the only difference that the VR group is presented with audio narratives accompanied by virtual relaxing environments, while the non-VR group only hear the narratives.

The protocol will follow the following schema:

- Session one: the therapist clearly explains the patient the role of bodily arousal in the maintenance of anxiety and underlines the fact that relaxation procedures can be useful to reduce the autonomic arousal. A general description of the method used in the following sessions will be given to the patient. After an oral presentation, patients will receive a short written description of the rationale. In this way, they will have the possibility to read the text as many times as they want, to ask questions about unclear points and to study it at home.

The following is an example of the text given to the patients (adapted from Ost, 1987):

"When a person suffers from an excessive anxiety usually manifests three different components in his/her reaction: physiological (increased heart rate, blood pressure, sweating etc.), behavioral (trying to escape from the anxious situation, trembling etc.), and subjective (negative thoughts like 'I am going to faint or lose control' etc.). The strength of these components varies between patients, but previous research has found that most people experience some physiological changes, followed by a negative thought, which increases the physiological reaction, generating a vicious circle.

One good way of breaking this development is to focus on the physiological reactions and learn not to react so strongly. The method we are going to use to achieve this is called applied relaxation. The aim of this technique is to learn a skill of relaxation, which can be applied very rapidly and in any real-life situation. This skill can be compared to any other skill, e.g. learning to swim, ride a bike, or drive a car, in that it takes time and practice to be learned, but once you have mastered it, you can use it anywhere. You are not restricted to the calm and non-stressful situation in the therapist office or your own home.

The goal of the treatment is to be able to relax in few sessions and to use this skill to counteract, and eventually get rid of, the physiological reactions you usually experience in anxious situations. To achieve this we are going through a gradual process starting with tensing and relaxing different muscle groups.

The next step teaches you to connect the self-instruction 'Relax' to the bodily state of relaxation. After that it is time for the rapid relaxation, which you practice many times a day in non-stressful situations. Finally, you reach the stage of applying the skill in anxious situations, and I will take you to different anxiety-arousing situations coaching you how to apply the relaxation at the first signs of anxiety in these situations. Applied relaxation is thus a skill that most people can acquire with the right instructions and practice. It is a 'portable' skill that can be used in almost any situation, e.g. when having problems in falling asleep.

During the entire protocol you'll be guided by relaxing narratives (and images) that suggest you how to reach a relaxed state".

The second part of the session one will be dedicated to fill the following questionnaires: PSWQ, BAI, AnTi, CID and STAI.

The following sessions will be dedicated to teach patients to recognize early signals of nervousness and to cope with anxiety. Each session lasts about one hour and is divided in four parts: homework checking, relaxation, comments about the experience (debriefing) and new homework assignments. Immediately before and after the relaxation phase physiological and psychometric measures will be taken in order to measure the objective and subjective effects of relaxation on the patient. The relaxation setting consists in a very quite room scarcely enlighten in which the patient sits in a comfortable armchair.

Sessions 2–5: during these sessions different narratives [27,28] guide patients in muscle relaxation. Using the "Emotioneering" approach [29], in the VR group the relaxing narrative will be linked to the presentation of the Green Valley.

Sessions 6–9: in these sessions the focus is on the breathing other than on the muscle relaxation. Again, in the VR group, the relaxing narrative will be linked to the presentation of the Green Valley.

Sessions 10–13: after nine sessions and weeks of homework practice, patients are ready to start applying the relaxation skill in stressful situations. During these last sessions a gradual exposure to feared situations is introduced so that patients can practice their applied relaxation skills. The exposure will be different for the two experimental groups. The VR group will be presented a virtual environment representing one of the situation that most frequently elicits anxiety in the patient, while patients in the non-VR group will use imaginal exposure to imagine real-life situations that usually provoke high level of anxiety.

Session 14: this session is devoted to the final debriefing. The patient and the therapist discuss about the results obtained with relaxation. Patients are encouraged to develop the habit of practice relaxation at least once a day. They are also encouraged to record their continued practice on a specific form during the first 6 months after the end of the treatment and to mail it regularly to the therapist.

During the entire treatment, patients are given different kind of homework assignments useful to increase their awareness during the every-day life and not only in the therapist's office. The first assignment consists in self-observation: patients are asked to record their anxiety reactions and to recognize and describe each situation that provokes them. In particular, between the sessions 2 and 5 patients are asked to fill a form including only Date, Situation and Intensity of the anxiety reaction (see figure 5). Between the sessions 6 and 9 they also have to fill a column called "Reaction" (that means: What did you fell?) and between the sessions 10 and 13 another column called "Action" (What did you do?) will be also included. The second assignment consists in practicing relaxation at least once a day using the portable audio-visual device they have received from the therapist. Every time they practice relaxation, they are asked to fill another form registering at what time they have practiced, how relaxed they were before and after the practice, how long it took them and eventually which difficulties they have experienced (see figure 6).

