### Aim of the study

Knowing that relaxation techniques are as effective as cognitive and behavioural methods in the treatment of GAD and considering the critical point regarding the difficult in learning them, the aim of the present study is to investigate the advantages of using a VR-based relaxation protocol in reducing anxiety in patients affected by GAD. The following hypothesis will be tested:

I) GAD patients exposed to a VR relaxing environment learn how to relax themselves easier and more efficiently than patients exposed to a traditional relaxation protocol;

II) There is a positive correlation between the treatment efficacy and the sense of presence experienced by the patients during the treatment sessions.

3-D audio-visual experiences, whose critical aspect is to induce a feeling of presence and engagement, will be presented to the subjects in order to help them to become relaxed. Through the link between the feeling of presence and the emotional state, VR relaxing environments will be used to reduce the anxiety levels in their users [15].

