## Discussion

Despite a large number of studies showing the advantages of using VR for the treatment of anxiety disorders (for a recent review see [30]), up to date there is only one study about its potential in stress management and relaxation processes in a sample of non-clinical stressed subjects [15]. What we would like to show with the present study is that VR can facilitate the reduction of anxiety even in a sample of GAD patients. We believe that the use of immersive VR for relaxation represents a promising approach since it enhances the quality of the relaxing experience through the elicitation of the sense of presence. In fact, as reported by different studies [31-34], individuals who interact in environments enriched with a variety of positive visual and auditory stimulations, report greater improvement in self-efficacy and mood. Being able to become relaxed in a certain situation promotes the sense of self-efficacy and prepares participants to cope with real anxiety situations.

Our outcome measures are well-suited to measuring both the subjective and objective impact related to the intervention and the presence of a non-VR group and of a WL list group will guarantee that the results eventually found are really attributable to the intervention. This controlled trial will be able to evaluate the effects of the use of VR in relaxation while preserving the benefits of randomization to reduce bias. Its design takes into account the need for internal and external validity and that the results are attributable to the intervention. Since the international scientific community is now starting to widely recognize the potential of VR as clinical tool [35] we look forward to adding the results of this trial to the growing body of literature in this area.

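### The protocol says the active arms differ only in the VR relaxing environment, but sessions 10–13 also differ in exposure mode, so questionnaire contrasts compare whole packages and cannot isolate the effect named in hypothesis I

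*Protocol article*

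**What the plan says.** All references are to the protocol article.

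- **Hypothesis I** (Aim of the study): "GAD patients exposed to a VR relaxing environment learn how to relax themselves easier and more efficiently than patients exposed to a traditional relaxation protocol". The general aim just before it is broader and concerns a VR-based relaxation protocol for reducing anxiety.
- **Stated difference between the active arms** (Clinical protocol, opening): sessions are the same, "with the only difference that the VR group is presented with audio narratives accompanied by virtual relaxing environments".
- **Sessions 10–13** (Clinical protocol): "The exposure will be different for the two experimental groups". In one arm, "The VR group will be presented a virtual environment representing one of the situation that most frequently elicits anxiety in the patient"; in the other, "patients in the non-VR group will use imaginal exposure to imagine real-life situations that usually provoke high level of anxiety". The section on the virtual environment software also assigns stressful virtual scenes to the second part of the protocol. The legend of Figure 4 places them in the final week.
- **Questionnaires** (Psychometric assessment): PSWQ, BAI, AnTI, CID and STAI are given before treatment, at completion, and at 6 and 12 months.
- **Session-level measures**: Psychometric assessment says "Immediately before and after each treatment session subjects will be also asked to rate their levels of subjective anxiety", and Psychophysiological assessment uses the same session window for physiology. Clinical protocol says instead: "Immediately before and after the relaxation phase physiological and psychometric measures will be taken".
- **Claim** (Discussion): the non-VR and waiting-list groups "will guarantee that the results eventually found are really attributable to the intervention".

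**The concern.** Hypothesis I is about one ingredient, a calm virtual environment that helps patients learn to relax. A contrast of two randomized arms speaks to one ingredient only if the arms differ in nothing else by the time the outcome is measured. The opening of the Clinical protocol section says this is so; the description of sessions 10–13 says it is not.

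A reader who relies on the opening sentence would take a better PSWQ or STAI score in the VR arm at completion as evidence that the relaxing environment works. The same result could come partly or wholly from practising in virtual rather than imagined feared situations. Randomization does not help, because both ingredients are assigned together. What is at stake is the wording of the trial's main conclusion.

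**Working it through.** The plan gives no figure on this point, so the check is a comparison of texts, some counting and one identity.

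**1. Do the two statements agree?** The opening of Clinical protocol allows one difference in session content, relaxing environments with the narratives. Sessions 10–13 use feared situations, which are not relaxing environments, and deliver them virtually in one arm and by imagination in the other. The statements are incompatible.

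The home device also differs (video and sound against sound only). Experimental design, however, names audio-visual mobile narratives as part of the VR condition, and the opening sentence is about sessions. That is not a second contradiction.

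**2. How much of the treatment differs in exposure mode?** Session 1 is explanation and questionnaires, and session 14 is debriefing. Training sessions are 2–13: 13 − 2 + 1 = 12. Exposure sessions are 10–13: 13 − 10 + 1 = 4. The share is 4/12 = 33% of training sessions, or 4/14 = 29% of all sessions.

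The Figure 4 legend does not fit this. At 2 sessions per week for 7 weeks, evenly spaced, session k falls in week k/2 rounded up:
- session 10: week 5
- sessions 11 and 12: week 6
- sessions 13 and 14: week 7

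Exposure in sessions 10–13 therefore runs over weeks 5 to 7. Read literally, the legend leaves only session 13 as an exposure session, or 1/12 = 8% of training sessions.

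**3. Which outcomes come before the exposure sessions?**
- Questionnaires: baseline only. Readings between session 9 and session 10: none. All three post-baseline occasions (completion, 6 months, 12 months) come after exposure.
- VAS-A and physiology: taken in every session, so they exist for sessions 2–9, which are 9 − 2 + 1 = 8 sessions before exposure starts.

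**4. What does each contrast estimate?** Write R for the effect of the VR relaxing material, E for the effect of virtual rather than imaginal exposure, and J for any interplay between them.
- VR minus non-VR on a questionnaire, at completion or later: R + E + J.
- VR minus non-VR on VAS-A or physiology in sessions 2–9: R alone, on that outcome.

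The first line is one equation with more than one unknown. The waiting-list arm does not resolve it: (VR − WL) − (non-VR − WL) is again VR − non-VR. Nor can the second line be subtracted from the first, because the outcomes differ.

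**5. Is the session-level window clear?** A session has four parts: homework check, relaxation, debriefing and new assignments. Readings around the session span all four; readings around the relaxation phase span one. The two descriptions define different measurements, and this matters because these data alone isolate the relaxation part.

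**The case against.** The strongest reply is that exposure is not foreign to the treatment. The text given to patients presents use of the skill in anxious situations as the last stage of applied relaxation, and sessions 10–13 are introduced as practice of that skill. The aim concerns a VR-based relaxation protocol, the comparator in hypothesis I is itself a protocol, and the Discussion attributes results to the intervention as a whole. On that reading the end-of-treatment contrast answers the question asked. **This stands** for the broad aim: the contrast is a valid comparison of packages. It does not rescue the opening sentence of Clinical protocol, nor a conclusion about the relaxing environment as such.

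A reader might infer more than the document supports:

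- **That hypothesis I cannot be tested.** It can, on session-level data from sessions 2–9.
- **That those data have no role in the plan.** The article does not say so. Experimental design counts psychometric and psychophysiological outcomes as dependent variables, and Trial analysis covers change in both. Which sessions serve which hypothesis may be left to an analysis plan that is not shown.
- **That hypothesis II is spoiled by pooling presence scores over calm and stressful scenes.** The article says when presence is measured, not how it is summarized. Hypothesis II relates presence to treatment efficacy across the treatment sessions, and exposure sessions are among them.
- **That the rate of misattribution can be stated.** Any such percentage would be the power of a 25-against-25 test under an assumed exposure effect, with the further assumption that VR relaxation adds nothing.
- **That eight sessions per patient multiply the sample.** They are repeated measures on 25 patients per arm.

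One reservation about the session data also stands: a rating taken straight after VR may reflect a momentary state rather than a learned skill.

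**Conclusion.** The concern holds in limited form. The account of how the active arms differ contradicts itself. If sessions 10–13 run as described, VR against non-VR differences on all five questionnaires, at all three post-baseline occasions, estimate the effect of the whole VR package. They cannot isolate the VR relaxing environment of hypothesis I.

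The size can be given only as a count: 4 of 12 training sessions differ in exposure mode, and no questionnaire reading precedes them. The numerical contribution of exposure to any questionnaire difference is unknown. The conclusion needs no assumed effect size and does not depend on the sample size calculation. It would fall away if, once the passages are reconciled, exposure turned out to be the same in both arms.

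The randomized comparison itself is sound. What needs changing is what it is said to show.

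**What to change.** 1. Reconcile the opening statement of Clinical protocol with sessions 10–13 and with the section on the virtual environment software, and reconcile the Figure 4 legend with sessions 10–13. Treatment content stays as it is.
2. State that end-of-treatment and follow-up contrasts of VR with non-VR estimate the effect of the whole VR package, and word the Discussion to match.
3. Base the relaxation-specific test of hypothesis I on VAS-A and physiology from sessions 2–9. Compare the two active arms with a repeated-measures model, with patient as the independent unit. Report both the average arm difference and the arm × session trend. A constant VR advantage from session 2 would show no trend, so the trend alone is not enough.
4. Do not adjust for pre-session values that earlier sessions could have changed. From session 3 on they may already carry the learning of interest. Subtracting them in a change score raises the same difficulty, so a pre-to-post change should be described as the within-session effect. Any baseline covariate should predate training, such as the session 1 questionnaires.
5. Reconcile the measurement window in Psychometric assessment and Psychophysiological assessment (around the session) with that in Clinical protocol (around the relaxation phase).

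The cost is a narrower claim for the end-of-treatment contrast and a little more analysis. No new data are needed.
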